### Status

Data collection is complete, but analysis has not yet started.

#### Study 2: Exploring How Much STOP Was Used in an RCT, and by Whom

### Overview

This mixed methods study will use STOP trial routine data and will conduct secondary analyses of qualitative data generated from interviews with STOP users who consented to data archiving. The interviews were originally conducted as part of a qualitative evaluation of the host STOP trial or other research work, and not as part of the planned process evaluation, and have been previously disseminated as peer-reviewed publications [30,31].

### Aims

To summarize how much STOP was used in an RCT, to characterize users of STOP, and to describe factors that predicted or influenced its use.

### Participants

Participants include 182 trial participants who were randomized to the intervention arms, and 10 STOP intervention users consenting to participate in interviews for data archiving. The eligibility criteria for trial participants are described earlier (in the Efficacy RCT section). No exclusion criteria were added to participate in the interview studies, although STOP users needed an email account and access to a phone or computer to take part [30,31]. Interviewees were predominantly female (15/25, 60%) and White (16/25, 64%) [30].

### Recruitment

The recruitment procedure for the host STOP trial is described earlier (in the Efficacy RCT section). In the qualitative studies, 2 samples participated in a one-off interview. The first sample comprises 8 participants who had completed the host STOP trial, were randomized to an intervention arm, provided informed consent for an optional qualitative interview, and consented to data archiving [30]. The second sample included 12 participants who were ineligible for the host trial but had tested a 6-week version of the STOP intervention on a dedicated study phone and consented to a one-off interview; the 2 participants who consented to data archiving will be included in our analyses [31].

### Measures

Measures will include intervention use, predictors of use, and factors that hindered or facilitated use. Intervention use in the trial is the primary outcome of study 2 and will be quantified and treated as a count variable based on the number of sessions completed (0-6 or 0-12) for 6 or 12 weeks, which was electronically monitored by a digital health platform (HealthMachine; Avegen Health). Acceptable and target session completion was defined in the study protocol as the user entering a response on 20 (50%) or 30 (75%) training items per session, and both completion rates will be considered.

Predictors of use will be selected from 10 quantitative variables in STOP trial routine baseline data. Our selection was informed by available trial data and an existing digital engagement model [32]. The digital complexity model proposes a person-centered approach to treatment and is informed by established models of engagement [32], such as the cumulative complexity model [33] and has been adopted in other evaluations [34]. Predictors include user variables (life demands, resources, and clinical characteristics) and STOP intervention variables (delivery device and therapy burden). User life demands include self-reported employment and marital status. User clinical characteristics include self-reported number of years living with paranoia, self-reported paranoia severity measured using a validated clinical measure (the Paranoia Worries Questionnaire) [35], and interpretation bias severity measured using the Similarity Rating Task. We selected the most sensitive measures of paranoia and interpretation bias severity as predictors after observing data in the host trial. User resources include self-reported dyslexia and premorbid IQ measured using the Wechsler Test of Adult Reading [36]. Intervention components include the STOP delivery device (users’ own smartphone or a study-provided phone) and intervention length (6 or 12 weeks, based on the allocated trial arm), both recorded in electronic databases used for the trial (MACRO; Ennov and HealthMachine).

Barriers to intervention use will be identified from qualitative self-reported reasons for lack of use from 3 sources. First, users reported reasons for missed sessions during check-in calls with a trained researcher. Second, reasons for withdrawal from the host trial are recorded in an electronic database (MACRO). Third, pooled interviews with STOP users will be used to identify whether any factors that hindered use were reported outside of routine trial data.

Facilitators to intervention use will also be identified from pooled interviews with STOP to determine whether any factors that facilitated intervention use were reported outside of routine trial data.

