### What Is Successful Treatment of Paranoia?

While other DMHIs for paranoia have been developed, most are delivered via virtual reality, require clinical support, or focus on other psychotic experiences (eg, voices) and pay limited attention to more common, social evaluative concerns within paranoia (eg, that others are talking about you negatively) [10]. Successful Treatment of Paranoia (STOP) was developed to address these limitations by providing a self-delivered, smartphone-based transdiagnostic intervention specifically targeting interpretation biases underpinning paranoia. The intervention and its development have been described in detail elsewhere [11,12]. A brief description is included to contextualize our work.

STOP is a self-administered psychological intervention using the principles of cognitive bias modification for paranoia (CBM-pa). CBM-pa aims to address the cognitive interpretation bias that is thought to cause and maintain the symptoms of paranoia [13]. Individuals displaying this interpretation bias often interpret neutral or ambiguous social scenarios as personally threatening [13]. There is preliminary evidence from a feasibility randomized controlled trial (RCT) that interpretation biases can be modified by CBM-pa that was delivered via a desktop computer in a research laboratory setting (N=63) [14].

STOP in the RCT included a weekly session administered through a smartphone app either on users’ personal smartphones or, if needed to avoid digital exclusion, on a study phone with a data plan provided free of charge to participants. Two versions of the intervention of varying lengths were evaluated to investigate “dose” effects (6 vs 12 weeks). Users scheduled weekly sessions at convenient times, during which they read 40 everyday social scenarios. In the sessions, users were encouraged to interpret ambiguous social scenarios in a nonthreatening way by completing a word puzzle and then answering a question about the meaning of the scenario (Figure 1 includes an intervention example). Session content was designed by clinicians, academics, and the McPin Foundation research charity’s STOP lived experience advisory panel (LEAP) of 7 people who give voice to intended end users of the app to increase its clinical relevance and acceptability to users [11]. Automated phone and email reminders were sent at midnight 1 day before the scheduled session and again if a session was not completed on the scheduled day.

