### Analysis

Quantitative analyses will be conducted using relevant packages in the most recent version of R. To contextualize the substudy findings, STOP users will be characterized using descriptive statistics, including clinical and sociodemographic variables, taken from the trial’s main outcome paper and supplemented as necessary by further information, and reported per intervention arm. Chi-square tests or pairwise comparisons will be used to test for differences between groups. To report intervention use, descriptive statistics will summarize the total number and proportion of intervention users in the host trial completing 0 to 6 or 0 to 12 sessions using acceptable and target rates. To test predictors of engagement, we will first assess the nature of the distribution and then run a linear regression analysis for normally distributed data or Poisson or negative binomial regression if data are not normally distributed (depending on overdispersion in the data). We will qualitatively analyze self-reported barriers and facilitators to intervention use using the same approach in study 1 (in the Analysis section) as analysis will be led by CH, supported by NVivo, and will deductively use the CFIR framework [29] in framework analysis [27,28], while inductively coding other data not captured in the initial framework.

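### Study 2 models raw session counts with no denominator, so the intervention-length coefficient carries the 2:1 difference in sessions offered and cannot be read as therapy burden

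*Protocol article*

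**What the plan says.** The Protocol article fixes three things for Study 2.

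- **Outcome.** Under Measures, use of the app is Study 2's primary outcome, "treated as a count variable based on the number of sessions completed (0-6 or 0-12) for 6 or 12 weeks". The description of the intervention says "STOP in the RCT included a weekly session administered through a smartphone app", so the allocated arm alone sets the maximum.
- **Predictors.** Under Measures: "Predictors of use will be selected from 10 quantitative variables in STOP trial routine baseline data". Those named include "intervention length (6 or 12 weeks, based on the allocated trial arm"; the intervention variables are described there as delivery device and therapy burden.
- **Model.** Under Analysis, the plan is to look at the outcome's shape first and afterwards "run a linear regression analysis for normally distributed data or Poisson or negative binomial regression if data are not normally distributed", with the last choice depending on overdispersion.

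The article mentions no offset, binomial model, proportion of sessions offered or separate model per arm. The one proportion given is descriptive: "total number and proportion of intervention users in the host trial completing 0 to 6 or 0 to 12 sessions". That is a proportion of users, not of sessions.

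**The concern.** Sessions completed out of 6 and sessions completed out of 12 are different scales. Pooling the raw counts and regressing them on length makes the length coefficient a blend of how many sessions were offered and how well people kept to them. Only the second is informative about burden. A longer programme that people abandon more readily can still appear as a positive predictor of use. Study 2's predictors are later combined with the qualitative themes and inform the implementation framework, so the result could influence how STOP is delivered.

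There is a second, smaller issue. Linear, Poisson and negative binomial models all ignore the ceiling. When most people complete most sessions, the variance falls below the Poisson variance. A check for overdispersion alone does not pick that up.

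**Working it through.** The article gives no sample size, power or effect figure for this analysis, so there is no stated figure to reproduce.

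**Inputs.** Maxima of 6 and 12 (Study 2, Measures); one session a week (description of STOP); total sample from Study 2, Participants: "Participants include 182 trial participants who were randomized to the intervention arms". The split is not given; 91 per arm is assumed in the simulations. Completion rates are not given either, so ranges are used. The expected ratios in steps 1 to 3 do not depend on the split.

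**Step 1: general form.** Let p6 and p12 be the proportions of offered sessions completed. The expected raw ratio is 12·p12 / (6·p6) = 2·p12/p6. It falls below 1 only if p12 < p6/2. The linear coefficient, 12·p12 − 6·p6, changes sign at the same point.

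**Step 2: particular values.**
- Equal completion: ratio 2.0. The linear difference is 6p: 3.0, 4.2 and 5.4 sessions at p = 0.5, 0.7 and 0.9.
- 80% versus 60%: 12 × 0.6 = 7.2 and 6 × 0.8 = 4.8, so the ratio is 7.2/4.8 = 1.5 in favour of 12 weeks. The odds ratio for completing a session is (0.6/0.4)/(0.8/0.2) = 1.5/4 = 0.375, in the opposite direction.

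**Step 3: attrition.** With constant weekly dropout h and full completion until dropout, the mean is the sum of (1−h)^k for k = 1 to 6 or 1 to 12. The ratio is therefore 1 + (1−h)^6.

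| Weekly dropout | Mean, 6 weeks | Mean, 12 weeks | Raw ratio | Proportion completed, 6 / 12 weeks |
|---|---|---|---|---|
| 0% | 6.00 | 12.00 | 2.00 | 1.00 / 1.00 |
| 2% | 5.59 | 10.55 | 1.89 | 0.93 / 0.88 |
| 5% | 5.03 | 8.73 | 1.74 | 0.84 / 0.73 |
| 10% | 4.22 | 6.46 | 1.53 | 0.70 / 0.54 |
| 20% | 2.95 | 3.73 | 1.26 | 0.49 / 0.31 |

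The proportion completed is lower at 12 weeks in every row with dropout, yet the raw ratio is always above 1.

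**Step 4: simulation** (beta-binomial sessions, 91 per arm, one other covariate).
- Equal completion of 50%, 70% or 90%: the Poisson rate ratio for length was 2.00 and significant in 100% of runs. A binomial model of sessions out of those offered, with robust standard errors, gave odds ratios of 1.01 to 1.03 and rejected in 4% to 6% of runs.
- Completion of about 80% versus 62%: the Poisson rate ratio was 1.55 in favour of 12 weeks, significant in 100% of runs. The binomial odds ratio was 0.41, significantly below 1 in 99%.

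**Step 5: what an offset changes.** Write L = 1 for 12 weeks. Then log(sessions scheduled) = log 6 + L·log 2, which is a linear function of L. Adding it as an offset lowers the intercept by log 6 and the length coefficient by log 2, and leaves every other coefficient as it was. In the simulation the length rate ratio moved from 2.00 to 1.00 and the covariate's coefficient did not change.

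**Step 6: dispersion.** For a beta-binomial count out of m with within-person correlation r, variance/mean = (1−p)(1 + (m−1)r).
- p = 0.85, r = 0.15: 0.15 × 1.75 = 0.26 for m = 6 and 0.15 × 2.65 = 0.40 for m = 12, averaging 0.33. Simulated Poisson type I error for an unrelated covariate was about 0.2% (nominal 5%). Power for a log-odds effect of 0.25 per SD was 17%, against about 65% with quasi-binomial.
- p = 0.75, r = 0.3: 0.25 × 2.5 = 0.625 and 0.25 × 4.3 = 1.075, averaging 0.85. Poisson type I error was 4.5%, so there was little harm.

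The ceiling is also visible in the fitted distribution: a Poisson mean of 4.5 puts 16.9% probability above 6 sessions, and a mean of 9 puts 12.4% above 12.

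**The case against.** **The count is the estimand.** Study 2 asks how much STOP was used, and use is defined as sessions completed. If 12-week users complete more sessions, a positive coefficient is correct for that question. This stands for absolute use, which the descriptive tables already show by arm. It does not rescue the regression, where length is a burden variable and the article does not separate exposure offered from burden.

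**The scaling is transparent.** In a log-link model a reader can halve the rate ratio (2.0 becomes 1.0; 1.5 becomes 0.75). True, but the reported test and confidence interval would still be against the wrong null, and the linear option has no such conversion.

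**The rest of the analysis survives.** A reader might infer that every predictor's estimate is biased. Step 5 shows otherwise for log-link models that include length. The others are touched only under the linear model, or if length is dropped when predictors are selected.

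**False positives.** A reader might also infer inflated type I error, since always using Poisson gives about 18% at 60% completion with correlation 0.5. The plan does not do that: dispersion there is about 2.0, and the article's rule would move to negative binomial, which brings the rate down to roughly 2% to 4%. With a switch at dispersion above 1.2 (an assumed cut-off), rates were 0.3% to 5.2% over completion of 60% to 85% and correlation of 0.15 to 0.5. What remains is conservatism.

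**The Open Science Framework plan may add a denominator.** It is not shown and might. The article nevertheless states outcome, predictor and model families outright, so this is a stated choice and not an omitted detail.

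**Conclusion.** The point holds for the length coefficient and, to a lesser degree, for the dispersion check. As written, the model cannot show lower adherence over 12 weeks unless the proportion completed is less than half that at 6 weeks. The expected ratio is 2.0 at equal completion, 1.89 to 1.26 with 2% to 20% weekly dropout, and 1.5 at 80% versus 60%.

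It would go too far to say that 12 weeks must show exactly twice the use. What is built in is the 2:1 ceiling; the factor of two needs equal per-session completion, and the article gives no completion data. The loss of power for other predictors is likewise conditional: marked near the ceiling, slight at 75% completion with correlation 0.3. The rejection rates and power figures assume 91 per arm and beta-binomial sessions. No efficacy or safety conclusion of the host trial depends on this analysis, but it is the primary outcome of Study 2.

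**What to change.** - Define the outcome as sessions completed out of sessions scheduled (y of 6 or y of 12), under both the acceptable and the target definition of a completed session.
- Prespecify one model: beta-binomial, or quasi-binomial logit with robust standard errors. A count model is also adequate if it has offset log(sessions scheduled) and robust standard errors that allow for under- as well as overdispersion.
- State that length is interpreted as an effect on the proportion completed.
- Drop marginal normality of the outcome as the criterion for choosing the model.
- Keep the 0-6 and 0-12 descriptive tables for absolute use.

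The cost is a wording change in the analysis plan and a different model call in R, with no new data. Odds ratios or completion-rate ratios replace raw rate ratios. The abstract describes Study 2 analysis as ongoing, while the Study 2 Status section says it has not started. In either case, make the change with a date before results are reported.

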### Procedure: Qualitative Interviews

A semistructured topic guide was created for each qualitative study (Supplementary Materials S1 and S2 in Multimedia Appendix 3). The topic guides were developed to explore users’ experiences of a digital therapeutic relationship [30] and the perceived acceptability of STOP [37]. Trained researchers (TT and LE) conducted all one-off interviews online, which were recorded and transcribed. Anonymized transcripts will be accessed from secure institutional servers.

### Analysis

Quantitative analyses will be conducted using relevant packages in the most recent version of R. To contextualize the substudy findings, STOP users will be characterized using descriptive statistics, including clinical and sociodemographic variables, taken from the trial’s main outcome paper and supplemented as necessary by further information, and reported per intervention arm. Chi-square tests or pairwise comparisons will be used to test for differences between groups. To report intervention use, descriptive statistics will summarize the total number and proportion of intervention users in the host trial completing 0 to 6 or 0 to 12 sessions using acceptable and target rates. To test predictors of engagement, we will first assess the nature of the distribution and then run a linear regression analysis for normally distributed data or Poisson or negative binomial regression if data are not normally distributed (depending on overdispersion in the data). We will qualitatively analyze self-reported barriers and facilitators to intervention use using the same approach in study 1 (in the Analysis section) as analysis will be led by CH, supported by NVivo, and will deductively use the CFIR framework [29] in framework analysis [27,28], while inductively coding other data not captured in the initial framework.

### Status

Data collection is complete, but analyses have not yet started.

#### Study 3: Qualitatively Exploring the Hypothetical Posttrial Implementation of STOP

### Overview

This qualitative study conducted interviews and focus groups with health care professionals and will conduct secondary analyses on interviews with STOP users (described under study 2).

### Aim

To identify the hypothetical barriers and facilitators to implementing STOP after the trial using the perspectives of STOP users and health care professionals.

### Participants

Participants include STOP users and health care professionals. The STOP user participants are described previously (in the Participants section for study 2). Twenty health care professionals from 6 NHS trusts in England participated in an interview (n=11) or focus group (n=2). These participants were aged 26 to 61 (mean 38, SD 11.736) years and were predominantly clinical psychologists (15/20, 75%), female (15/20, 75%) and White (16/20, 80%).

### Recruitment

The recruitment processes for STOP users are described earlier (in the Recruitment section for study 2). Health care professionals were recruited from NHS trusts in England. Participants were those who provided informed consent to take part in a one-off interview or focus group after trialing a tester version of the STOP intervention or had viewed a video demonstrating the app.

### Procedure

The procedure for the STOP user interviews has been described previously (in the Procedure section for study 2). The health care professional topic guide was developed to explore the perceived acceptability of STOP (Supplementary Material S3 and S4 in Multimedia Appendix 3). Trained researchers (CH, AK, and HS) conducted the interviews and focus groups using Microsoft Teams, which were recorded and transcribed.

### Analysis

Descriptive statistics for anonymized basic demographic data will be tabulated. To date, interviews and focus groups have been transcribed verbatim. Next, we will qualitatively analyze data using the same approach in study 1 (in the Analysis section) with analysis led by CH, supported by NVivo, and deductively using the CFIR framework [29] in framework analysis [27,28], while inductively coding other data not captured in the initial framework.

### Status

Data collection and transcription are complete, and preliminary analyses have started.

#### Integrating Qualitative and Quantitative Data

Integration of quantitative and qualitative findings will be undertaken using a triangulation approach guided by the CFIR framework [29]. Integration will occur at the interpretation and reporting stages through a joint comparison of quantitative indicators (eg, predictors) and qualitative themes on barriers and facilitators. Quantitative and qualitative data will be synthesized within the CFIR framework [29] to identify key barriers and facilitators to implementing STOP in and after a trial (process evaluation aim 2). Therefore, our process will identify convergent and divergent findings and provide an evidence-based understanding of factors influencing implementation using mixed methods data.

#### Patient and Public Involvement

Patient and public involvement in the STOP trial is contributed via the LEAP, coordinated by the McPin Foundation, and is described in more detail in the protocol paper [12]. Within the process evaluation, the LEAP contributed to developing the health care professional topic guide, provided input on the process evaluation design, and a lived experience peer researcher collected and transcribed data in study 3.

#### Process Evaluation Deliverables and Dissemination Plan

We expect 2 deliverables from the process evaluation: (1) a research report and (2) a hypothetical implementation framework. First, we will report the process evaluation in an implementation paper. Second, our findings will generate a hypothetical implementation framework for the delivery of STOP after the trial, which will include implementation strategies that are tailored to delivering STOP both inside and outside mental health services. Both deliverables will be reviewed by the STOP LEAP, and disseminated as peer-reviewed, open-access journal articles and conference presentations. Our work will also be disseminated to potential end users through existing connections via the McPin Foundation’s networks, the STOP LEAP, and other relevant end user networks.

